### Study treatment

Subjects randomized to MIPS will have the intervention performed as close to the time of randomization as possible. Study protocol requires subjects to enter the OR within 24 h from last known normal (LKN), with a goal of arrival in the OR within 8 h. MIPS is to be performed in accordance with the study surgical manual (Supplementary Datasheet 1). All surgically randomized cases are video recorded, with the first two surgical cases from each site reviewed by the study's lead neurosurgeon (GP) to objectively assess adherence to the surgical protocol. Following surgery, care will follow the Clinical Standardization Guidelines (CSG) for management (Supplementary Datasheet 2).

In the standard treatment arm, subjects will be treated according to the CSG. The decision for surgical intervention with an external ventricular drain for CSF diversion or ICP control/monitoring, decompressive craniectomy, clot evacuation using traditional techniques, or both is left to the treating neurosurgeon. As traditional surgical techniques, such as decompressive hemicraniectomy, remain available to the treating team in the standard management arm, cross-over from this arm to MIPS is strictly not permitted.

### Post-randomization in-hospital assessment

General neurologic evaluation, as assessed by the NIHSS and the GCS, will be monitored daily for the first 7 days following randomization. General laboratory and neuroimaging performed per routine medical care will be collected during this time. A daily checklist will be completed to identify clinical parameters that may be uncorrected and inconsistent with the CSG for care.

### Post-discharge follow up

The outcomes battery includes mRS, NIHSS, GCS, and Health Utilities Index (HUI). The full in-person outcomes battery will occur at 180 days (± 14 days) post-randomization. This assessment will be conducted with both the subject and the primary caregiver/family member to corroborate subject responses. The mRS will also be collected on day 30 (± 7 days) and day 90 (± 14 days) via telephone communication. The 30, 90, and 180-day mRS are audio recorded for blinded adjudication. The 30, 90, 120, and 180-day HUI will be collected by telephone unless visit is conducted in person.

### Primary efficacy analysis

The primary efficacy endpoint is the UWmRS scale at 180 days post-randomization (Table 3). The primary analysis will be performed on all subjects randomized in the ENRICH study. Subjects will be analyzed according to the group they are randomized to, referred to as the intent to treat population. Let Δ be the mean difference in UWmRS between treatment groups (MIPS—standard management) in the ITT population, in which a positive value indicates MIPS benefit.

**Table 3 T3:** mRS values to utility weights mapping.

**mRS**	**Utility weights**
0	1.0
1	0.91
2	0.76
3	0.65
4	0.33
5	0
6	0

The following hypothesis will be tested:

H_0_: Δ ≤ 0, i.e., the mean difference in UWmRS between treatment groups is ≤0H_1_: Δ> 0, i.e., the mean difference in UWmRS between treatment groups is >0.

If the Bayesian model-based posterior probability of MIPS benefit (i.e., Δ> 0) is ≥0.975, then the study will demonstrate superiority of MIPS vs. standard management.

### Adaptive sample size and enrichment plan

A trial update will be performed when the number of patients enrolled is equal to 150, 175, 200, 225, 250, and 275 patients. The purpose of the trial updates is to determine whether one or two ICH locations meet futility criteria, or whether the current sample size is sufficient to achieve success on the primary outcome. At each trial update, one of the following three decisions will be made:

1) Stop accrual to patients with ICH in either ABG, Lobar, or both locations due to futility.a. If accrual stops in only one of the two locations, this creates population enrichment.b. If accrual stops in both locations, the trial is stopped for futility.

2) Stop accrual of all patients due to expected success in the pooled ABG/Lobar population. If enrollment is stopped due to expected success, the primary analysis will occur 180 days after the last patient is enrolled.3) Continue accruing patients without changes.

If the trial does not stop for futility, the primary analysis will occur 180 days after the last patient is enrolled. If enrichment takes place at any point in the trial, and subsequently the primary analysis criteria are met, superiority is only claimed for the location that did not meet the futility criteria, despite the final evaluation including patients from both locations.

In order to stop accrual within a location due to futility, the following two criteria must be met:

1) The Bayesian model-based probability of a clinically meaningful difference (a mean difference of UWmRS of at least 0.075) between surgery and control is <0.20.2) At least 30 patients have complete 180-day outcomes within the location.

To trigger stopping of accrual for expected success, two criteria must be met:

1) The Bayesian model-based probability of a difference in mean UWmRS utility is ≥0.99.2) At least 60 patients have completed 180-day outcomes.

### Statistical modeling

The primary analysis will be based on a pre-specified Bayesian hierarchical model which assumes a constant treatment effect across hemorrhage locations, but in which the mean UWmRS in the control group may differ between locations. Missing data will be addressed via Bayesian multiple imputation, in which 90-day UWmRS values are used to inform the likelihood of 180-day values for patients with missing 180-day UWmRS outcomes. The interim updates will incorporate two models: (1) a model equivalent to the primary analysis model for monitoring expected success in the overall study population; and (2) a Bayesian hierarchical model in which the treatment effect is allowed to vary between hemorrhage locations for the purpose of monitoring futility. Both models used in the interim updates will incorporate longitudinal modeling, in which 90-day UWmRS values are used to inform the likelihood of 180-day values for patients with incomplete information.

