## Methods and analysis

### Study objective

The primary objective of the ENRICH trial is to determine if early ICH evacuation using MIPS results in improved outcomes for patients with an ICH. The primary hypothesis is that MIPS will result in an improvement in the 180-day utility-weighted modified Rankin Scale (UWmRS) when compared to patients treated with standard guideline-based management. To address the primary objective, we have designed an adaptive clinical trial with a sample size between 150 and 300 subjects, with frequent interim analyses to determine if early stopping rules are met and if patient population enrichment per hemorrhage location should occur. Randomization between MIPS and standard management groups will be equal and patients will be block randomized by ICH location, anterior basal ganglia (ABG) vs. lobar location as well as Glasgow Coma Score (GCS) with a threshold for stratification <9 vs. ≥9. At each interim analysis, the enrollment scheme defined by hemorrhage location can be adapted based on the *a priori* enrichment plan.

Secondary aims of the study will evaluate the economic and clinical benefits, and the safety of MIPS compared to standard management. The clinical benefit of MIPS is thought to be a function of clot removal while minimizing white matter injury. Therefore, we will determine if the percent volume of ICH reduction is associated with improved UWmRS at discharge, 30, and 90 days between the treatment groups. The economic effect of MIPS for ICH will be evaluated by quantifying the cost per quality-adjusted life-year (QALY) gained through MIPS at 30, 90, 120, and 180 days. Safety of MIPS will be assessed: (1) by determining the effect of MIPS on mortality when compared to standard management at 30 days; (2) by assessing post-operative rebleeding associated with clinical deterioration following MIPS. Rebleeding will be defined by a growth in hemorrhage volume between an initial non-contrast head computed tomography scan (NCCT) and a follow-up NCCT obtained within 24 h of the index NCCT. Lastly, we will evaluate the impact of time from onset of symptoms to MIPS on the UWmRS.

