### Study design and method

ENRICH is an adaptive, two-arm, randomized comparative effectiveness study, where eligible patients are block randomized by ICH location (ABG vs. lobar) and GCS to early ICH evacuation using the MIPS approach plus standard management vs. standard guideline-based management alone. Scheduled interim analyses, beginning after 150 patients have been enrolled, will guide the adaptive sample size and study enrichment (Figure 1). A maximum of 300 subjects will be enrolled.

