**Figure 2 F2:**
[figure not shown]
Subject flow chart.

The IOC will review eligibility criteria and the patient's clinical information (Table 2). Once the patient meets eligibility criteria and informed consent has been obtained from the patient or legally authorized representative, the subject may be randomized using the central electronic data capture (EDC) portal.

**Table 2 T2:** Inclusion and exclusion criteria.

Study inclusion criteria	• Age 18–80 years • Pre-randomization head CT demonstrating an acute, spontaneous, primary ICH • ICH volume between 30 and 80 ml as calculated by the ABC/2 method • Study intervention can reasonably be initiated within 24 h after the onset of stroke symptoms. If the actual time of onset is unclear, then the onset will be considered the time that the subject was last known to be well • Glasgow Coma Score GCS 5–14 • Historical Modified Rankin Score 0 or 1

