### Sample size justification

Virtual trial simulations were used to quantify the statistical power and Type I error (Supplementary Datasheet 3). With an adaptive sample size of 150–300 subjects and a base “expected” set of assumptions regarding patient accrual, dropout, distribution of mRS for control and treatment groups, prevalence of ABG/Lobar locations, and treatment benefit in either one or both locations, the Bayesian primary analysis has approximately 90% or greater power for detecting superiority of treatment vs. control for a mean UWmRS difference in both ABG/Lobar locations of 0.15 or larger (i.e., a 15% absolute increase in utility weighted mRS), with an approximate one-sided Type I error <0.025. In addition, the trial design and analysis provide approximately 60–90% power for detecting treatment superiority if there is a mean benefit on UWmRS of 0.15 or larger in one of the two locations.

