### Secondary endpoints

The secondary endpoints were selected to provide supportive information on safety and efficacy. These secondary endpoints include:

Postoperative rebleeding associated with deterioration following MIPS (no hypothesis test).ICU and in-hospital length of stay (two-sided *t*-test).mRS at discharge, 30 and 90 days (ordinal logistic regression; treatment as explanatory variable).Impact of percent ICH reduction with MIPS on mRS at 180 days (ordinal logistic regression; %ICH reduction as explanatory variable).Impact of end-of-treatment (EOT) volume with MIPS on mRS at 180 days (ordinal logistic regression; EOT volume as explanatory variable).Proportion of patients with mRS at 180 days equal to 0, 1, 2, or 3 (chi-square test).Ordinal mRS at 180 days (Wilcoxon rank sum test).Overall survival through 180 days (log-rank test and Cox proportional hazards model).

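### GCS is a randomisation stratum, but the primary and interim models as described adjust for location only, and the named secondary and safety tests use neither stratum; the result is a conservative analysis with a modest loss of power

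*Protocol article*

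**What the plan says.** Under Study objective, patients are "block randomized by ICH location, anterior basal ganglia (ABG) vs. lobar location as well as Glasgow Coma Score (GCS) with a threshold for stratification" at <9 versus ≥9. Study design and method repeats that "eligible patients are block randomized by ICH location (ABG vs. lobar) and GCS". The inclusion criteria admit "Glasgow Coma Score GCS 5–14", so both GCS strata can be populated.

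Under Statistical modeling, the primary model "assumes a constant treatment effect across hemorrhage locations, but in which the mean UWmRS in the control group may differ between locations". The interim model for expected success is described as equivalent to it. The interim model for futility differs in letting the treatment effect vary by location. GCS is not mentioned in that section. Sample size justification lists the simulation assumptions; the prevalence of the two locations is among them, but nothing about GCS is.

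Success is declared when the "posterior probability of MIPS benefit (i.e., Δ> 0) is ≥0.975", and the design is reported "with an approximate one-sided Type I error <0.025".

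Secondary endpoints names the analysis of early outcomes as "mRS at discharge, 30 and 90 days (ordinal logistic regression; treatment as explanatory variable". It also names a chi-square test for mRS 0–3, a Wilcoxon rank sum test for ordinal mRS, a log-rank test with a Cox model for survival, and a t-test for length of stay. Primary safety objective names Pearson's chi-square test and a t-test or Wilcoxon test. None is described as stratified or adjusted.

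**The concern.** When randomisation is balanced on a prognostic factor, the treatment estimate varies less between hypothetical repetitions of the trial. A model without that factor leaves its variance in the residual and reports the larger uncertainty that simple randomisation would have produced. Analysis and design then do not match, and the benefit of stratifying is partly wasted.

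The 0.975 success rule, the 0.99 expected-success rule and the location futility rule all read a posterior probability. If the posterior is too wide, success is somewhat harder to declare than intended. Accrual can stop from 150 patients, where there is less precision to spare than at 300.

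**Working it through.** **The plan's own figure.** The stated power is about 90% or greater for a difference of 0.15, with 150–300 patients and one-sided 0.025. It comes from simulations of an adaptive design. The article gives no SD, mRS distributions or dropout rate, so it cannot be reproduced exactly. As a fixed-sample plausibility check with 1:1 allocation, the largest SD compatible with 90% power is 0.15 / [(1.960 + 1.282) × √(4/N)]:

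- N = 300: 0.401
- N = 150: 0.283

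At N = 300, power is 96.0%, 92.8% and 90.1% for SD 0.35, 0.38 and 0.40. The stated power is therefore plausible near the maximum size without any GCS term.

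**Inputs that must be assumed.** The share q of patients with GCS <9 (20–40%), the UWmRS gap d between strata (0.15–0.25) and the SD (0.33–0.36) are not in the document.

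**Variance explained by the stratum.** R² = q(1−q)d²/SD².

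- Low: 0.2 × 0.8 × 0.15² / 0.36² = 0.028
- Middle: 0.3 × 0.7 × 0.20² / 0.33² = 0.077
- High: 0.4 × 0.6 × 0.25² / 0.33² = 0.138

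**Two standard errors.** Without GCS, the model reports SE = SD√(4/N). Under stratified randomisation the true SE is k times that, with k = √(1−R²) = 0.986, 0.961 and 0.929.

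**True one-sided error of the unadjusted rule.** 1 − Φ(1.96/k) = 0.023, 0.021 and 0.017. All are below 0.025.

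**Patients' worth of lost power.** For 90% power the required N is proportional to (1.960 + 1.282k)² without the GCS term and to (3.242k)² with it.

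| R² | without GCS | with GCS | ratio | extra patients per 300 |
|---|---|---|---|---|
| 0.028 | 3.224² | 3.196² | 1.017 | 5 |
| 0.077 | 3.191² | 3.114² | 1.050 | 15 |
| 0.138 | 3.150² | 3.010² | 1.095 | 29 |

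**Power for a difference of 0.15.** Without GCS it is Φ[(0.15 − 1.96·SE)/(k·SE)]; with GCS it is Φ[0.15/(k·SE) − 1.96].

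| R² (SD) | N = 150, without / with | N = 300, without / with |
|---|---|---|
| 0.028 (0.36) | 72.6% / 73.5% | 95.3% / 95.5% |
| 0.077 (0.33) | 80.4% / 82.6% | 98.0% / 98.4% |
| 0.138 (0.33) | 81.2% / 85.0% | 98.3% / 98.9% |

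Over a wider grid (SD 0.35–0.40, R² 0.05–0.20), the gain from adding GCS is about 0.4–3 points at 300 and about 2–8 points at 150.

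**Location futility rule.** Accrual stops if P(Δ ≥ 0.075) < 0.20. With a flat prior and no borrowing, the chance of stopping is Φ[(0.075 − 0.842·SE_model − Δ)/SE_true]. Take 60 patients in a location, SD 0.35 and R² 0.077. Then SE_true is 0.0868, and SE_model is 0.0904 without GCS and 0.0868 with it.

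- True Δ = 0.15: stops 4.1% without GCS, 4.4% with it.
- True Δ = 0: stops 49.5% without GCS, 50.9% with it.

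Omitting GCS makes futility stops slightly rarer in both cases.

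**The case against.** The strongest objection is that a condensed article need not list covariates. The modelling section explains how location enters because location drives the enrichment; it never says that location is the only term. This stands as a limit: the full analysis plan may contain GCS, so the point applies to the models as described. It does not remove the point. The simulation assumptions also mention location and not GCS, and the secondary and safety tests are named outright in unadjusted form, including an ordinal model with treatment as the explanatory variable.

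It is also fair that the secondary endpoints are supportive, so stratified versions are an improvement and not the correction of an error.

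A reader might infer more than the document supports:

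- **That a strong predictor is dropped at large cost.** The article does not quantify the prognostic strength of GCS. Choosing it as a stratum suggests only that the designers thought it mattered.
- **That the loss is 9–48 patients.** That is what 300/(1−R²) − 300 gives for the same inputs. It compares model variances and ignores the balance that stratification already provides; the comparison above gives 5–29.
- **That futility calls become noisier.** The estimate is unchanged in variability; only its stated uncertainty is too wide, so futility stops become slightly more conservative.
- **That type I error or the stated power is wrong.** The error is below nominal, and the stated power is plausible without a GCS term.

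**Conclusion.** The point holds as a mismatch between design and described analysis. It costs efficiency and does not threaten validity. The size depends on assumed values for the SD, the share with GCS <9 and the gap between strata. At the maximum sample size the power difference is under one percentage point on the main assumptions and at most about 3 on the wider grid. It matters more if accrual stops near 150. The calculations use a normal approximation with fixed N and no dropout, so they show direction and order of magnitude, not the operating characteristics of the adaptive Bayesian design. Because the analysis plan is not at hand, the conclusion is conditional on that plan having no GCS term.

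**What to change.** First confirm whether GCS enters the primary and interim models. If it does not:

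- Add the GCS stratum, or baseline GCS itself, as a main effect in the primary model and in both interim models. On the mean-difference scale this leaves the target Δ unchanged.
- For the secondary and safety comparisons between arms, use versions that account for location and GCS: an adjusted ordinal model, van Elteren in place of Wilcoxon, Mantel-Haenszel in place of chi-square, and a stratified log-rank test.

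GCS is already assessed before randomisation, so no new data are needed. The cost is a rerun of the simulations, with a stated GCS prevalence and effect, and the need to fix the change before any unblinded look.

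Timing matters. Study organization and funding refers to the interim analyses in the past tense. If they have been run, the primary model should stay as pre-specified, and the GCS-adjusted model should be reported as a sensitivity analysis that is itself specified before the final data are unblinded.

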### Sample size justification

Virtual trial simulations were used to quantify the statistical power and Type I error (Supplementary Datasheet 3). With an adaptive sample size of 150–300 subjects and a base “expected” set of assumptions regarding patient accrual, dropout, distribution of mRS for control and treatment groups, prevalence of ABG/Lobar locations, and treatment benefit in either one or both locations, the Bayesian primary analysis has approximately 90% or greater power for detecting superiority of treatment vs. control for a mean UWmRS difference in both ABG/Lobar locations of 0.15 or larger (i.e., a 15% absolute increase in utility weighted mRS), with an approximate one-sided Type I error <0.025. In addition, the trial design and analysis provide approximately 60–90% power for detecting treatment superiority if there is a mean benefit on UWmRS of 0.15 or larger in one of the two locations.

### Primary safety objective

The primary safety objectives will be evaluated by the rate of mortality and/or rebleeding at 30 days, which will be compared between the two groups using a Pearson's chi-square test and the difference in hemorrhage volume between index CT and 24-h follow-up CT, which will be compared between the two groups using a two-sided *t*-test (or Wilcoxon rank sum test if the normality assumption is violated).

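### The primary safety rate pools 30-day deaths with rebleeding, so the 30-day mortality question has no stated analysis of its own and a rebleeding difference can be diluted

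*Protocol article*

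**What the plan says.** The section Study objective numbers two safety assessments. The first is "by determining the effect of MIPS on mortality when compared to standard management at 30 days". The second is "by assessing post-operative rebleeding associated with clinical deterioration following MIPS". Rebleeding is defined there as growth in hemorrhage volume between the initial scan and "a follow-up NCCT obtained within 24 h of the index NCCT".

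The section Primary safety objective evaluates these objectives by "the rate of mortality and/or rebleeding at 30 days", "which will be compared between the two groups using a Pearson's chi-square test". It adds a second measure, "the difference in hemorrhage volume between index CT and 24-h follow-up CT", compared by t-test or Wilcoxon test.

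Among the Secondary endpoints, rebleeding appears as "Postoperative rebleeding associated with deterioration following MIPS (no hypothesis test", and mortality as "Overall survival through 180 days (log-rank test and Cox proportional hazards model". The section Safety monitoring has the DSMB receive group comparisons in which mortality and rebleeding are separate items.

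**The concern.** Two questions are asked and one pooled answer is planned. The first question, the effect of MIPS on 30-day mortality, cannot be read off a rate that also counts rebleeding. The reverse also holds: where deaths are much more frequent than rebleeds, the pooled rate mostly reflects deaths, and a difference in rebleeding adds little to it.

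A null pooled result would therefore not tell a reader whether neither component differed, whether rebleeding differed but was swamped, or whether the two components offset each other. For an invasive procedure these are different safety conclusions. The primary efficacy analysis is not affected.

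There is also a mismatch of time windows. The pooled rate is set at 30 days, while the only definition of rebleeding given rests on a CT within 24 hours of the index CT.

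**Working it through.** **Inputs from the article.** Total sample size 150 to 300 with equal allocation (Study objective), so 75 to 150 per arm. Early mortality after ICH in general 35% to 52% (Introduction). The article gives no expected safety event rates, no alpha and no power for the safety comparison, so there is no stated figure to reproduce.

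**Assumptions.** Two-sided alpha 0.05. All arm-level event rates below are assumed for illustration.

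**Step 1. Which question has an analysis?**

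| Question | Analyses stated | What is left open |
|---|---|---|
| 30-day mortality, MIPS vs standard | Pooled 30-day rate; 180-day survival; 30-day mRS | No comparison of 30-day mortality itself |
| Rebleeding with deterioration after MIPS | Secondary endpoint, described without a test | Nothing: objective and endpoint agree |
| Rebleeding between arms | Pooled 30-day rate; 24-hour volume difference | No comparison of rebleeding itself |

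**Step 2. Form of the pooled rate.** With death probability D and rebleeding probability R in an arm, the pooled rate is D + R if no patient has both, and 1 − (1 − D)(1 − R) if the two are independent. With no overlap, the arm difference is the sum of the two component differences, so opposite signs subtract.

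Power for two proportions with n per arm and difference d is Φ((d − 1.96·SE0)/SE1) plus the opposite tail, with SE0 = √(2·p̄(1 − p̄)/n) and SE1 = √((p1(1 − p1) + p2(1 − p2))/n).

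**Step 3. Dilution with no mortality difference.** Mortality 35% in both arms, rebleeding 2% standard vs 12% MIPS.

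| | Standard | MIPS | Power, 150 per arm | Power, 75 per arm |
|---|---|---|---|---|
| Rebleeding alone | 2% | 12% | 93% | 67% |
| Pooled, no overlap | 37% | 47% | 42% | 24% |
| Pooled, independent | 36.3% | 42.8% | 21% | 13% |

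For the first row at 150 per arm: p̄ = 0.07, SE0 = 0.0295, SE1 = 0.0289, and (0.10 − 1.96 × 0.0295)/0.0289 = 1.46, which gives 93%.

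**Step 4. Cancellation, if deaths moved the other way.** At 150 per arm with no overlap:

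- Standard: 60 deaths (40%) + 5 rebleeds (3.3%) = 65 (43.3%).
- MIPS: 48 deaths (32%) + 17 rebleeds (11.3%) = 65 (43.3%).
- Pooled: 65/150 vs 65/150, p = 1.00.
- Rebleeding: pooled proportion 22/300 = 0.0733, SE = √(0.0733 × 0.9267 × 2/150) = 0.0301, difference 0.080, z = 2.66, p about 0.008.
- Deaths: pooled proportion 108/300 = 0.36, SE = √(0.36 × 0.64 × 2/150) = 0.0554, difference 0.080, z = 1.44, p about 0.15.

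**Step 5. Range.** At 150 per arm, with control mortality from 20% to 52%, opposing differences of 5 to 10 points, and either overlap assumption, the pooled test rejects in 5% to 10% of trials. A test of rebleeding alone has 38% to 93% power.

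**The case against.** **The wording may mean separate tests.** The section speaks of objectives in the plural and writes and/or. But it names one rate and one chi-square test, which reads as a composite. If separate tests were meant, a primary safety measure is open to two readings, and the same edit settles it. A fuller protocol or a SAP may report the components. That is no answer to text that positively fixes a pooled measure for questions asked separately.

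**The second safety objective is already served.** This stands. Post-operative rebleeding with deterioration is an assessment in the MIPS arm with no natural control counterpart, and describing it without a test fits the objective. It should not be turned into a between-arm test.

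**The components are visible elsewhere.** Largely true. The DSMB sees them by group, 180-day survival is tested, and the 30-day mRS includes death as grade 6. A rebleeding excess would not be hidden from safety oversight during the trial. None of these, however, is a stated final estimate of the 30-day mortality effect or of the rebleeding difference. Nor does the 24-hour volume comparison isolate rebleeding: in MIPS patients scanned after surgery, evacuation itself lowers the volume.

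**The tempting stronger reading.** A reader might infer that opposing effects are to be expected, with deaths falling because evacuation is life-saving and rebleeds rising because of the procedure. The article does not support this. Where the Introduction and the rationale on cross-over speak of life-saving surgery, they mean conventional techniques, which are open to both arms. The eligibility rationale ties the life-saving role to clots above 80 ml, which the trial excludes. The Introduction reports early experience that MIPS prevents rebleeding.

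**The cancelling example is constructed.** It is. The two differences were set equal with no overlap, and the 40% comes from a range for ICH in general, whereas the trial excludes several groups with very poor prognosis. It shows that cancellation is possible, not that it is likely. Dilution does not depend on it.

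**Conclusion.** The point holds in this form: the objectives ask about 30-day mortality and rebleeding separately, the primary safety analysis on its plain reading pools them, and the 30-day mortality effect is left without a stated analysis. That follows from the text alone.

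The size of the loss rests on assumed rates. With equal mortality of 35% and rebleeding of 2% versus 12%, power at 150 per arm falls from 93% to between 21% and 42%. With offsetting deaths it falls close to the significance level. Neither the direction of the mortality effect nor the rebleeding rates can be taken from the article.

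This is worth correcting because it changes what the trial can conclude about safety. It does not affect the efficacy conclusion, and it does not mean that harm would go unseen by the DSMB.

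**What to change.** In the section Primary safety objective, replace the single rate by two between-arm comparisons, each reported with a risk difference and 95% CI:

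- (a) all-cause mortality at 30 days;
- (b) rebleeding, under one definition and one time window that apply to both arms.

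For (b), reconcile the 30-day window in this section with the 24-hour CT definition in Study objective. Keep the composite, if wanted, as a supplementary summary. Leave post-operative rebleeding with deterioration as the descriptive MIPS-arm item among the secondary endpoints.

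The cost is one additional safety comparison, plus a decision on the rebleeding definition. Mortality and rebleeding are already presented to the DSMB by group, so no new data collection appears necessary for a 24-hour definition. If a 30-day window is kept for rebleeding, the source of later imaging should be confirmed, because the section Post-randomization in-hospital assessment describes collecting routine imaging for the first 7 days.
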